### Safety outcomes and adverse events (AEs)

AEs will be continuously checked during the 7-day treatment period. AEs indices will include all adverse events. At any time, all information about adverse events, including their severity, duration, and correlation to SHHS granules, should be recorded in detail. The AEs was graded as mild, moderate, or severe. Mild AEs could be defined as situations that could be tolerated without any further medical therapies. Moderate AEs is pain or discomfort that patients can not tolerate and require medical treatments. Severe AEs means that, after receiving the medications used in the study, the patients have a dead, life-threatening, permanent, or severe disability or loss of function; the patients need hospitalization or extended hospitalization or lead to congenital abnormalities or birth defects. AEs must be reported to the research center, principal sponsor, and research medical ethics committee as soon as possible. At the same time, the National Medicinal Product Administration (NMPA) will be notified within 24 h. A serious adverse event must also be completed as soon as possible.

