### Withdrawal criteria and termination criteria

First, the investigator's decision to withdraw the patient is based on the following principles: 1) during the clinical trial, the patients develop diseases that are not suitable for further study; 2) patients with adverse events or serious adverse events are not suitable to continue the study, and 3) other conditions that the researchers believe will harm the health of the patients by continuing the study.

Second, patients can and should withdraw if they are unwilling to continue with the clinical trial. According to the provisions of the informed consent form, participants can withdraw at any time during the study. If patients have not explicitly proposed to withdraw but no longer accept medication and testing, as well as loss to follow-up, are regarded as 'withdrawal'. The reasons for withdrawal should be known and recorded as precisely as possible. Examples include consciously being unable to tolerate adverse events, inability to continue clinical research due to other reasons, or loss to follow-up without explaining the reasons. In electronic case report forms (eCRFs), the reasons for dropout will be recorded and the data analysis will include their last record.

Third, when reviewing the data prior to statistical analysis, it is up to the principal investigator (PI) and statisticians to judge whether an individual case is excluded. If one of the following events occurs, the two sides should consider whether the patient should be excluded based on the study's progress and the reasons for withdrawal and provide a detailed explanation: 1) After randomization, individuals not meeting the selection criteria or meeting the exclusion criteria of the research proposal are found; 2) The failure to take at least one dose of trial medication and the lack of any data post-randomization.

Fourth, the conditions for stopping early are as follows: 1) if a high incidence of serious adverse events is found during the research, the study should be suspended in time; 2) if during the research, significant mistakes are found in the research proposal or there are serious deviations in its implementation, making it difficult to evaluate the efficacy of drugs, the research should be stopped; 3) the ethics committee requests to suspend or terminate the research; 4) the administrative department cancels the research.

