### Interventions measures

Patients in the SHHS group will receive SHHS granules (10 g per bag), two bags at a time, three times a day, to be swallowed with warm water. The administration of LHQW granules (10 g per bag) will be the same as the SHHS group. The medication course was 7 days (the medication could be stopped in advance if the discharge standard was reached). It will be forbidden to receive other TCM for COVID-19 treatment during the treatment period, including TCM decoctions, granules, or proprietary Chinese medicine. The types, dosage, and cumulative time (including the start and end dates) of the combined therapy drugs should be recorded during the observation period. The intervention will be stopped if there are any severe adverse effects or withdrawal.

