### Analysis of safety outcomes

All participants in the safety set are examined during safety analysis. All AEs that occurred during the intervention period are recorded, including their type, severity, frequency, and relationship to the intervention medicine. The quantity and frequency of adverse events are calculated for both groups. Severe adverse events and consequent drug discontinuation are meticulously recorded. Safety analysis will use qualitative judgment to define the distribution, counting the number of participants and their fraction of abnormal indicators using cross-tabulation (Table 5). The correlation between AE and medications will be evaluated using standards from the 2011 Ministry of Health of the People's Republic of China's Measures for the Reporting and Monitoring of Adverse Drug Reactions.

**Table 5 T5:** Analysis of the adverse events in the full analysis set.

Adverse event	SHHS Group (n=xx)	LHQW Group (*n*=xx)	*P-Value*
In total^b^	xx(xx%)	xx(xx%)	.xx
Headache^b^	xx(xx%)	xx(xx%)	.xx
Nausea^b^	xx(xx%)	xx(xx%)	.xx
Vomiting^b^	xx(xx%)	xx(xx%)	.xx
Diarrhea^b^	xx(xx%)	xx(xx%)	.xx
Loss of appetite^b^	xx(xx%)	xx(xx%)	.xx

^b^Number, percentage.

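### The adverse event scale grades mild and moderate by intensity but severe by seriousness, so severity is misclassified in both directions and severe cannot be told apart from serious

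*Protocol article*

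**What the plan says.** All the definitions are in the protocol article, section Safety outcomes and adverse events (AEs). The scale has three levels: "The AEs was graded as mild, moderate, or severe". The lowest is "Mild AEs could be defined as situations that could be tolerated without any further medical therapies". The middle is "Moderate AEs is pain or discomfort that patients can not tolerate and require medical treatments". The highest begins "Severe AEs means that, after receiving the medications used in the study, the patients have a dead, life-threatening, permanent, or severe disability" and continues with loss of function, hospitalisation or a longer stay, and congenital harm. The section closes with a sentence on serious adverse events but gives no definition of *serious* apart from the one given for *severe*.

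Other sections use the two words for different purposes:
- Interventions measures: "The intervention will be stopped if there are any severe adverse effects or withdrawal".
- Withdrawal criteria and termination criteria, on suspending the study: "if a high incidence of serious adverse events is found during the research".
- Analysis of safety outcomes: "Severe adverse events and consequent drug discontinuation are meticulously recorded". The same section says that severity and relationship to the intervention medicine are recorded for every event.

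On causality, the safety outcomes section asks for "correlation to SHHS granules, should be recorded in detail" and does not mention LHQW.

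**The concern.** Intensity (how bad the event is for the patient) and seriousness (whether it led to one of a list of outcomes) are different properties. A severe headache may not be serious, and a minor event can be serious if it keeps the patient in hospital. A scale that measures intensity on its first two levels and seriousness on its third does not order events on either property.

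Safety is part of the trial's stated aim. The safety analysis calls for severity on all events and singles out severe ones. If the top grade holds a different kind of event from the lower two, a reader cannot say whether one granule produced more intense reactions than the other. With no separate definition of *serious*, a reader also cannot tell whether the sections on stopping treatment, suspending the study and recording severe events refer to one category or two.

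**Working it through.** There is no figure in the plan to reproduce, so the check compares the definitions and then tests the direction of the error.

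**Step 1. Criterion used at each grade**

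| Grade | Criterion in the text | Property |
|---|---|---|
| Mild | tolerated, no treatment | intensity |
| Moderate | not tolerated, treated; no upper limit | intensity |
| Severe | death, threat to life, disability or loss of function, new or longer stay, birth defect | seriousness only |

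**Step 2. Two test events**

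- *Event A*: intolerable and treated, with none of the listed outcomes. It fits moderate. However intense it is, nothing in the severe definition admits it, so it is graded down.
- *Event B*: low intensity, but it lengthens the hospital stay. It meets the severe definition, which asks nothing about intensity. If it needed no treatment it also fits mild, and the text gives no order of precedence. I assume the highest grade met applies, so it is graded up.

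Event B is realistic here. The Inclusion criteria require admission within the previous 24 hours, so patients are inpatients and the relevant hospital criterion is mainly a longer stay.

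**Step 3. Direction of the net error**

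Let S be the number of events severe by intensity, a the share of them that are not serious (graded down), and b the number of low-intensity events that meet a listed outcome (graded up). Then:

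recorded severe = S × (1 − a) + b

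net error = b − a × S

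All three inputs are assumptions; the documents give none of them. With S = 10:

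| a | b | Recorded severe | Net error |
|---|---|---|---|
| 0.5 | 0 | 10 × 0.5 + 0 = 5 | −5 |
| 0.5 | 5 | 10 × 0.5 + 5 = 10 | 0 |
| 0.2 | 5 | 10 × 0.8 + 5 = 13 | +3 |
| 0.8 | 0 | 10 × 0.2 + 0 = 2 | −8 |
| 0.2 | 8 | 10 × 0.8 + 8 = 16 | +6 |

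Over a from 0.2 to 0.8 and b from 0 to 8, the net error runs from −8 to +6. In the second row the total is correct, yet 5 of the 10 recorded events are the wrong ones. A net error of zero therefore does not mean correct grading.

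**Step 4. Use of the two terms**

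Stopping the intervention is tied to *severe*, and suspending the study to *serious*. The safety analysis singles out *severe*, and the safety outcomes section uses both. Only *severe* has a definition, and it consists of seriousness outcomes.

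**Step 5. Relatedness**

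The safety outcomes section names SHHS only. The safety analysis section refers to the intervention medicine, to counts in both groups, and to the correlation between events and medications. The first instruction is narrower than the second.

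**The case against.** The strongest defence is that *severe* is simply a rendering of *serious*, so the article has one concept throughout and the sections do not conflict in substance. That may be so. The three-level scale would then have no grade for severe intensity, and the severity data would still lack one. Either reading calls for a correction.

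A second defence is that a journal article condenses the full protocol. The eCRF is not shown, and the closing sentence on serious adverse events reads as if the name of a form had dropped out, so seriousness may be captured separately. This would excuse silence, but the article states a definition, and that definition misgrades events.

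Several points for the plan do stand:
- Table 5 lists event types only, so no severity comparison is displayed. Severity is recorded, and the article does not show how it will be reported.
- The investigator may withdraw a patient for an adverse event of any kind, so an intense non-serious event is not left without a route.
- Stopping one patient's treatment and suspending the study are decisions at different levels. Different words there are not in themselves a contradiction.
- A stay lengthened by discharge policy alone is not an adverse event and would not count.

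Three stronger readings are tempting but not supported:
- *Severity is understated.* Step 3 shows that the sign is not fixed.
- *Every severe count equals the serious count.* This needs a definition of *serious* that the article never gives.
- *Relatedness cannot be compared between arms.* The safety analysis section is wide enough to cover both drugs; the mismatch is one of wording between two sections.

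**Conclusion.** The point holds as a defect in a stated definition. The scale mixes intensity and seriousness, so events are misclassified in both directions, and severe and serious events cannot be told apart from the text. The amount and net sign of the error are unknown; the range of −8 to +6 per 10 intense events illustrates direction only and is not an estimate.

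The conclusion assumes that investigators grade as the article instructs and that the highest grade met applies. If the eCRF already holds separate intensity and seriousness items, the data may be sound and only the text needs correcting. The relatedness wording is a smaller, separate inconsistency. The primary and secondary efficacy analyses are not touched. The correction should be made, but it does not threaten the trial's main result.

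**What to change.** 1. Define mild, moderate and severe on one axis, by effect on the patient.
2. Record seriousness as a separate yes/no item for each event, using the outcomes now listed under severe.
3. Tabulate intensity and seriousness by arm, next to the event-type rows of Table 5.
4. Reconcile *severe* and *serious* in the sections on withdrawal and termination, interventions, safety outcomes and safety analysis. Which term governs stopping is for the sponsor and the investigator to decide.
5. Align the causality instruction with the safety analysis section, so that relatedness is recorded for the study drug received in both arms.

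The cost is a small change to wording and, if the eCRF lacks it, one extra item. Recruitment started in March 2022. Whether events already entered need review depends on what the eCRF captures, which the documents do not show.

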### Data collection, management, and quality control

An electronic data capture (EDC) system will gather and manage data in this trial. The electronic case report form (eCRF) data matches the information in the original medical records, laboratory examination reports, and other sources. According to the research protocol, the eCRF should guarantee that all the data required for analysis are collected efficiently and precisely. To maintain the quality of the data and guarantee adherence to the protocol, the sponsor and investigators will establish quality control and quality assurance systems, respectively. Investigators and research assistants who participate in clinical research must have professional expertise, qualifications, and abilities in clinical research. They should explicitly explain the protocols for patient selection, data input, medication use, AEs reporting, and dropout documentation. They should conscientiously and patiently explain to the patients to fully understand and cooperate with the research to provide good patient compliance. Patients should be informed of possible adverse reactions to the medication and the coping approach to be taken in the event of adverse reactions.

It is necessary to protect clinical research data's authenticity, integrity, and privacy and to guarantee the traceability of clinical research data. For the questions existing in the data, the data administrator will fill in the concentrator data-ready queue (DRQ) and send a query to the investigators through the clinical monitor. Investigators should answer this question and provide feedback as soon as possible. The data administrator will modify the data according to the investigators' answers, confirm and enter them, and send the DRQ again if necessary. Data verification includes computerized program verification (edit check), manual verification, and data verification meetings. Any inconsistent data (data query) found in the verification shall be corrected in time. The data department shall issue a discrepancy report and submit it to the researcher for confirmation and changes. At the end of the study, the researchers and statistical analysts will review the data and lock them after confirming that they are correct. All electronic data will be stored in password-protected files on designated computers that researchers can access. The necessary documents for this study shall be archived and managed in relevant drug clinical research institutions and statistical units, respectively. The research data shall be kept until five years after the end of the study.

## Statistical analysis plan

### Statistical methods

The statistical analysis plan will comply with the guidelines for the content of statistical analysis plans in clinical trials (Gamble et al., 2017). (**Additional File 3**). After finishing the trial, all statistical analysis tests will be conducted using SAS (version 9.4; SAS Inc., Cary, NC, USA) and one-sided tests with a nominal alpha level of 0.025. All confidence intervals (Cls) will be stated at the 95 confidence level. To assess non-inferiority, the CI lower limit of the difference between groups will be compared with a predefined non-inferiority limit. Non-inferiority could only be declared when the 95% CI lower limit of the difference between groups is not larger than the non-inferiority threshold of 10%.

Continuous outcomes will be described by calculating the mean, standard deviation, median, and minimum and maximum values. The means and standard deviations are reported for normal continuous data. For non-normally distributed continuous variables, the median and interquartile ranges are given. The frequency and proportion of each category are displayed as counting indications.

Between-group comparisons are performed using an independent two-sample t-test (normality, homogeneity of variance) or the Wilcoxon rank-sum test (non-normality, heterogeneity of variance). The paired t-test is used for comparisons within normally distributed groups, and the paired rank-sum test is used for comparisons within non-normally distributed groups. For count metrics, the χ^2^ test or Fisher's exact probability will be required, whereas, for categorical variables, the Wilcoxon rank-sum test will be utilized. Repeated measured outcomes are applied to a generalized linear mixed model analysis.

In patients where baseline indicators are unbalanced, an adjustment to the efficacy contrast of variables such as age, sex, and concurrent therapy is required. The covariance approach is employed for continuous variables, and for count or rank data, logistic regression analysis is performed.

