### Sample size

The study hypothesis is SHHS group will be non-inferior to LHQW group. Clinicians and statisticians set the non-inferiority threshold at 10% and predicted that the recovery rate of clinical symptoms after 7 days of LHQW is about 87% and that of SHHS is 90% according to the literature reports on similar drugs. It is estimated that 94 patients for each group, ie. a total of 188 patients are needed to achieve the power of 80% at a one-sided statistically significant level of 0.025. Considering the possible dropout rate of 20%, 240 patients will be enrolled, that is 120 patients for each group.

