### Analysis of primary outcome

The primary analysis will be conducted on the FAS and PPS, which is the rate of self-reported clinical symptoms, including fever, fatigue, and coughing recovery. The percentage of patients whose clinical symptoms disappeared on the seventh day will be summarized. CMH-Chisquare test will be applied to compare rates between groups and Clopper-Pearson method will be used to calculate the 95%CI for rate difference (Table 3).

**Table 3 T3:** Analysis of the primary outcome.

	Full analysis set				Per Protocol set			
Variables	SHHS group (n=xx)	LHQW Group (n=xx)	Rate difference 95%CI	*P-Value*	SHHS group (n=xx)	LHQW Group (n=xx)	Rate difference 95%CI	*P-Value*
Rate of clinical symptom recovery at days 7 (n,%)^b^	xx (xx%)	xx (xx%)	xx%(xx% to xx%)	.xx	xx (xx%)	xx (xx%)	xx%(xx% to xx%)	.xx

b Number, percentage.

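### The only non-inferiority decision rule shown has its inequality reversed, its minus sign missing and its order of subtraction unstated; probably a drafting error, but as worded it does not control the one-sided 2.5% error

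*Protocol article*

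**What the plan says.** The hypothesis is given under Sample size: "The study hypothesis is SHHS group will be non-inferior to LHQW group". The same section sets the margin without a sign ("Clinicians and statisticians set the non-inferiority threshold at 10" per cent) and gives the planning assumptions: "the recovery rate of clinical symptoms after 7 days of LHQW is about 87% and that of SHHS is 90" per cent, with enough patients "to achieve the power of 80% at a one-sided statistically significant level of 0.025". This leads to 94 per group, raised to 120 per group for dropout.

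The decision rule appears under Statistical methods. It is introduced by saying that "the CI lower limit of the difference between groups will be compared with a predefined non-inferiority limit", and then fixed as follows: success may be claimed only if "the 95% CI lower limit of the difference between groups is not larger than the non-inferiority threshold of 10" per cent.

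Under Primary outcomes, the endpoint is the proportion of patients whose symptoms have recovered at day 7. Analysis of primary outcome and Table 3 add a rate difference with a 95% interval and a chi-square comparison, but they do not restate a margin or a success condition. Nowhere does the article write minus 10%, and nowhere does it say which group is subtracted from which.

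**The concern.** For a beneficial outcome, the lower confidence limit is the relevant bound only when the difference is test minus control. On that scale the limit marks the largest loss of recovery that the data still allow, and non-inferiority means that this loss is smaller than the margin: lower limit above minus 10 points. The article asks instead for a lower limit at or below plus 10. Almost every possible result meets that condition, and it becomes harder to meet only as SHHS gets better.

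The sentence is the only success rule shown for the primary question. The Discussion ties its claims about SHHS to whether non-inferiority can be declared. The trial is also open-label, so a criterion that has to be reinterpreted leaves the choice of reading until after results may be known.

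**Working it through.** **Inputs.** LHQW 87%, SHHS 90%, margin 10 points, one-sided 0.025, power 80%, 94 evaluable and 120 enrolled per group (all from Sample size). Direction of benefit: higher is better (Primary outcomes).

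**1. Reproduce the planned size under the conventional test.** The null hypothesis is SHHS minus LHQW at or below −10 points, so the distance from the null to the planned effect is 0.03 + 0.10 = 0.13.

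n per group = (1.960 + 0.842)² × [0.87 × 0.13 + 0.90 × 0.10] / 0.13² = 7.849 × 0.2031 / 0.0169 = 94.3

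The article states 94, and power at 94 is 79.9%. For dropout, 188 / 0.8 = 235 against 240 stated. The design was therefore sized for success when the lower limit exceeds −10 points.

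**2. Apply the written rule to one example.** Take observed rates of 57% for SHHS and 87% for LHQW, 94 per group.

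SE = √(0.57 × 0.43/94 + 0.87 × 0.13/94) = 0.0617

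95% CI = −0.30 ± 1.96 × 0.0617 = −42.1% to −17.9%

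Since −42.1% is not larger than 10%, the written rule declares non-inferiority, although the whole interval lies beyond the 10-point margin.

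**3. Probability of declaring non-inferiority.** Exact enumeration over all pairs of binomial outcomes, Wald 95% limits, LHQW fixed at 87%, 120 per arm:

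| True SHHS recovery | Literal rule, SHHS − LHQW (lower ≤ +10%) | Literal rule, LHQW − SHHS (lower ≤ +10%) | Correct rule, SHHS − LHQW (lower > −10%) |
|---|---|---|---|
| 100% | 90.5% | 100% | 100% |
| 90% (planned) | 99.99% | 100% | 88.7% |
| 77% (at the margin) | 100% | 97.5% | 2.7% |
| 67% | 100% | 51.9% | 0.01% |
| 60% | 100% | 12.1% | about 0 |
| 57% | 100% | 4.7% | about 0 |

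With 94 per arm the pattern is the same. At 77% the three rules give 100%, 97.4% and 2.7%. At the planned 90% the correct rule gives 80.0%, matching the stated power.

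**4. Does repairing one element suffice?** No (94 per arm, SHHS − LHQW):
- Sign only (lower ≤ −10%): 97.3% at SHHS 77%, but only 20.0% at the planned 90%.
- Direction only (lower > +10%): 0.03% at the planned 90%, in effect a test for superiority by more than 10 points.

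Direction and sign must change together, and the order of subtraction must be stated.

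**The case against.** The strongest reply is that this is a slip of wording and nobody would run the trial this way. The Introduction hypothesises an effect no less than that of LHQW, the alpha level and the choice of a lower limit are the usual ones, and the sample size fits the conventional test. If 10% is read as the size of a shortfall, so that a negative lower limit may be at most 10 points below zero, the behaviour is nearly as intended: 2.7% at SHHS 77% and 88.7% at 90% with 120 per arm. Table 3 would also show the interval, so a gross failure would be visible. Most of this stands, and it makes a drafting error the likely explanation. But the sentence does not speak of size or absolute value. Taken strictly, an absolute-value reading would also refuse non-inferiority when the lower limit exceeds +10 points, that is, to a clearly superior product.

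A second reply is that the full analysis plan may state the rule correctly. It may. The point here, however, is an explicit statement that is wrong, not an omission left to a fuller document.

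Three stronger readings might be inferred and are not supported:
- *That the rule passes an arbitrarily inferior product whatever the scale.* This holds only for SHHS minus LHQW. With the order reversed, the probability falls to 12.1% at SHHS 60% and 4.7% at 57%. That rule is still invalid, because the upper limit would then be the relevant bound.
- *That the unsigned margin under Sample size is a second error.* Quoting a margin as 10% is ordinary usage. The fault lies in the comparison under Statistical methods.
- *That naming two analysis sets ("The primary analysis will be conducted on the FAS and PPS") without saying that both must succeed is part of this fault.* That text is neither false nor contradictory, and how the two sets combine may properly be left to the full plan.

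**Conclusion.** The decision rule under Statistical methods is misstated and should be corrected before analysis. Neither order of subtraction yields the one-sided 0.025 level that the same section sets: at the margin the literal rule declares non-inferiority about 100% of the time for SHHS minus LHQW and about 97% for the reverse, against about 2.7% for the correct rule. It also conflicts with the test that reproduces 94 per group.

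These figures assume LHQW recovery of 87%, 120 analysed per arm and Wald limits. Wald limits explain why the correct rule gives 2.7% and not 2.5%. At the margin the gap between the literal and the correct rule is far too wide for the interval method to matter. The figures describe the sentence as worded. They do not predict how the trial will be analysed, and the design itself is not shown to be unsound.

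**What to change.** Replace the sentence under Statistical methods with:

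> The difference is the recovery rate of SHHS minus that of LHQW; non-inferiority is declared only if the lower limit of the two-sided 95% CI is greater than −10 percentage points.

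If a separate analysis plan exists, check that it carries the same wording. The cost is one sentence in a dated amendment made before the data are analysed. Sample size, margin, alpha and conduct stay as they are. No rule on combining the FAS and PPS results needs to be added for this correction.

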### Descriptive statistics

Participants' baseline characteristics will be reported in a baseline table for each randomization group, and baseline data and descriptive statistics will be assessed using standard measures in accordance with the recommendations of the consolidated standards of reporting trials (CONSORT) guidelines (Moher et al., 2010). (Table 2). The table describes the following variables: age, sex, height, weight, clinical symptoms, and medical and treatment histories. The sample is displayed in accordance with the entire analysis set. Baseline characteristics will be compared between the groups.

**Table 2 T2:** Baseline demographic and clinical characteristics.

Variables	SHHS Group (n=xx)	LHQW Group (n=xx)	All participants (n=xx)	*P-value*
Age (year)^a^	xx (xx)	xx (xx)	xx (xx)	.xx
18≤Age<65	xx (xx)	xx (xx)	xx (xx)	.xx
Age≥65	xx (xx)	xx (xx)	xx (xx)	.xx
Males sex^b^	xx (xx%)	xx (xx%)	xx (xx%)	.xx
Height (cm)^a^	xx (xx)	xx (xx)	xx (xx)	.xx
Weight (kg)^a^	xx (xx)	xx (xx)	xx (xx)	.xx
Vital signs				
Heart rate (beats/minute)^a^	xx (xx)	xx (xx)	xx (xx)	.xx
Respiratory rate (breathe / minute) a	xx (xx)	xx (xx)	xx (xx)	.xx
Pulse Rate (beats/minute)^a^	xx (xx)	xx (xx)	xx (xx)	.xx
Systolic blood pressure (mmHg)^a^	xx (xx)	xx (xx)	xx (xx)	.xx
Diastolic blood pressure (mmHg)^a^	xx (xx)	xx (xx)	xx (xx)	.xx
Temperature (°C)^a^	xx (xx)	xx (xx)	xx (xx)	.xx
Past medical history^b^	xx (xx%)	xx (xx%)	xx (xx%)	.xx
Diabetes^b^	xx (xx%)	xx (xx%)	xx (xx%)	.xx
High blood pressure^b^	xx (xx%)	xx (xx%)	xx (xx%)	.xx
Coronary artery disease^b^	xx (xx%)	xx (xx%)	xx (xx%)	.xx
Chronic obstructive pulmonary disease^b^	xx (xx%)	xx (xx%)	xx (xx%)	.xx
Stroke^b^	xx (xx%)	xx (xx%)	xx (xx%)	.xx
Cancer^b^	xx (xx%)	xx (xx%)	xx (xx%)	.xx
Heart failure^b^	xx (xx%)	xx (xx%)	xx (xx%)	.xx
···	···	···	···	···
Disease diagnosis^b^	xx (xx%)	xx (xx%)	xx (xx%)	.xx
Mild^b^	xx (xx%)	xx (xx%)	xx (xx%)	.xx
Moderate^b^	xx (xx%)	xx (xx%)	xx (xx%)	.xx
Initial symptoms^b^				
Fever^b^	xx (xx%)	xx (xx%)	xx (xx%)	.xx
Cough^b^	xx (xx%)	xx (xx%)	xx (xx%)	.xx
Fatigue^b^	xx (xx%)	xx (xx%)	xx (xx%)	.xx
Diarrhea^b^	xx (xx%)	xx (xx%)	xx (xx%)	.xx
Shortness of breath^b^	xx (xx%)	xx (xx%)	xx (xx%)	.xx
Sore throat^b^	xx (xx%)	xx (xx%)	xx (xx%)	.xx
Nausea^b^	xx (xx%)	xx (xx%)	xx (xx%)	.xx
Vomiting^b^	xx (xx%)	xx (xx%)	xx (xx%)	.xx
Taste and smell dysfunction^b^	xx (xx%)	xx (xx%)	xx (xx%)	.xx
Loss of appetite^b^	xx (xx%)	xx (xx%)	xx (xx%)	.xx
···	···	···	···	···

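### Covariate adjustment of the efficacy contrast is triggered by undefined baseline imbalance, allows an undated concurrent-therapy covariate, and uses logistic regression without returning to the rate-difference margin

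*Protocol article*

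**What the plan says.** All references are to the protocol article.

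- **Adjustment rule (Statistical methods).** "In patients where baseline indicators are unbalanced, an adjustment to the efficacy contrast of variables such as age, sex, and concurrent therapy is required". The next sentence assigns a covariance method to continuous variables, and "for count or rank data, logistic regression analysis is performed".
- **How imbalance would be seen (Descriptive statistics, Table 2).** "Baseline characteristics will be compared between the groups". Table 2 has a P-value column. No P value or other cut-off is tied to the word unbalanced.
- **Concurrent therapy.** Under Interventions measures, the types, dosage and duration "of the combined therapy drugs should be recorded during the observation period". Table 1 has combined drugs at screening and on days 1 to 8. Table 2, the baseline table, also has a block for concomitant medications.
- **Decision scale.** The Sample size section states: "Clinicians and statisticians set the non-inferiority threshold at 10" per cent. Statistical methods compares the lower confidence limit of the between-group difference with that margin. Analysis of primary outcome and Table 3 give a rate difference with a 95% CI and a CMH test, and name no covariates.
- **Status of covariate models elsewhere.** The secondary-outcome text says only that logistic regression will be considered, to explore covariates. Statistical methods makes adjustment mandatory once imbalance is found.

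**The concern.** Three features of the rule leave the adjusted efficacy result poorly fixed.

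First, adjustment depends on what the baseline table shows. With no cut-off and an open list, two analysts could follow the rule and fit different models. If the adjusted and unadjusted results fall on opposite sides of the margin, the article does not say which one counts.

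Second, concurrent therapy is named as a covariate without a date. If it includes drugs started after randomisation, it can respond to the allocated arm and to the early course of illness. The Blinding section covers assessors and statisticians but does not mention treating staff. Conditioning on such a variable no longer estimates the effect of assignment.

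Third, the margin is a difference in rates, while the standard output of logistic regression is an odds ratio. No step converts one to the other.

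At stake is whether an adjusted analysis that the plan requires could support or contradict the non-inferiority conclusion with no rule to settle it.

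**Working it through.** **1. The plan's own scale.** Inputs: "the recovery rate of clinical symptoms after 7 days of LHQW is about 87% and that of SHHS is 90" per cent, a 10-point margin, "one-sided tests with a nominal alpha level of 0.025" and 80% power. With unpooled variance on the rate-difference scale:

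n = (0.87×0.13 + 0.90×0.10) × (1.960 + 0.842)² / (0.03 + 0.10)² = 0.2031 × 7.849 / 0.0169 = 94.3 per arm.

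The article states 94. Power at 94 per arm is 79.9%, so the figure reproduces, and the margin is a rate difference.

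**2. The margin as an odds ratio.** OR = [(p−0.10)/(1−p+0.10)] / [p/(1−p)], where p is the LHQW rate.

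| LHQW rate | OR equal to −10 points | Difference implied by a fixed OR of 0.50 |
|---|---|---|
| 80% | (0.70/0.30)/(0.80/0.20) = 0.58 | −13.3 points |
| 87% | (0.77/0.23)/(0.87/0.13) = 0.50 | −10.0 points |
| 95% | (0.85/0.15)/(0.95/0.05) = 0.30 | −4.5 points |

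No single odds-ratio limit stands in for 10 points.

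**3. Concurrent therapy, if it includes on-treatment use.** All inputs here are assumed. SHHS has 50% of patients on track early and LHQW 75%. Recovery is 97% if on track and 57% if not. Therapy has no effect; it is given to 10% of patients on track and 60% of the others.

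- True rates: SHHS 0.50×0.97 + 0.50×0.57 = 77%; LHQW 0.75×0.97 + 0.25×0.57 = 87%. Difference −10.0 points.
- Users: SHHS (0.05×0.97 + 0.30×0.57)/0.35 = 62.7%; LHQW (0.075×0.97 + 0.15×0.57)/0.225 = 70.3%. Difference −7.6.
- Non-users: SHHS (0.45×0.97 + 0.20×0.57)/0.65 = 84.7%; LHQW (0.675×0.97 + 0.10×0.57)/0.775 = 91.8%. Difference −7.1.
- Mantel-Haenszel weights: 0.35×0.225/0.575 = 0.137 and 0.65×0.775/1.425 = 0.354. Adjusted difference **−7.3 points**.
- With 80% use among those not on track, the same steps give **−5.2 points**.

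The direction is not fixed. In a simpler linear model, adjusted difference = −0.10 − e×d, where d is the excess use on SHHS and e the association of use with recovery. With d = 0.20, e = −0.20 gives −6 points and e = +0.20 gives −14 points.

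**4. Does the trigger inflate type I error?** Simulated at the margin: 0.87 against 0.77, 96 per arm (120 less 20% dropout), 3000 runs, one assumed normal baseline covariate with log-odds slope 0, 0.5, 1 or 1.5, and adjustment when P<0.05. Simulation error is about √(0.025×0.975/3000) = 0.3 percentage points.

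| Slope | Unadjusted | Triggered, standardised rate difference | Always-adjusted OR against 0.50 |
|---|---|---|---|
| 0 | 3.2% | 3.2% | 2.8% |
| 0.5 | 2.3% | 2.3% | 2.0% |
| 1 | 2.4% | 2.2% | 1.3% |
| 1.5 | 2.6% | 2.1% | 0.6% |

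No inflation from the trigger is visible. Testing the conditional odds ratio against 0.50 behaves as a different test from the 10-point comparison.

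**5. How often a trigger might fire.** If unbalanced meant P<0.05 and the tests were independent (both assumed), at least one would fire with probability 1−0.95²⁰ = 64% for 20 tests and 1−0.95³⁰ = 79% for 30. About 38 rows of Table 2 carry a P value, but several overlap, such as the age bands and mild with moderate. These figures show only that some trigger is likely. They are not error rates.

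**The case against.** The strongest defence is that the primary analysis is untouched: it is a rate difference with a 95% CI, the decision rule uses the between-group difference, and covariate models for secondary outcomes are only exploratory. A full analysis plan may also list covariates and describe standardisation. The first part stands and limits the point to the adjusted contrast. The second does not dispose of it, because the article states a rule and calls it required; the trouble is what that rule says.

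Four stronger readings are tempting and are not supported.

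- *Concurrent therapy is post-randomisation.* The sentence concerns baseline indicators, Table 2 lists concomitant medications as baseline, and Table 1 includes a screening record. The covariate is undated; it may be post-randomisation. That prescribing follows the patient's progress is inferred from the open-label design and not stated.
- *Adjustment would favour SHHS.* Under other assumed inputs the shift goes the other way.
- *The trigger inflates the error rate.* The simulation shows no visible inflation, and the article ties imbalance to no P value.
- *Logistic regression cannot be used against the margin.* Only the raw odds ratio cannot. A logistic model standardised to a marginal rate difference can.

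**Conclusion.** The point holds as one of poor pre-specification. Adjustment is mandatory on an undefined condition, with an open covariate list and no statement of which result decides non-inferiority. Concurrent therapy is not restricted to use before randomisation. If on-treatment use is included, the adjusted contrast could move by several points in either direction: a true −10 became −7.3 or −5.2 in one assumed scenario and ranged from −6 to −14 in another. These sizes illustrate the risk and do not predict this trial. The scale mismatch is arithmetic: 10 points is an odds ratio of 0.50 only at the planning rate of 87%. The sample size and the stated primary test are unaffected. The change should be made, but the trial's conclusion does not fail without it.

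**What to change.** Before the data are unblinded:

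1. Remove the imbalance trigger. Pre-specify one adjusted analysis with a fixed set of baseline variables already collected, for example mild or moderate class, age and baseline symptoms, used whatever imbalance is seen.
2. Drop concurrent therapy as a covariate or restrict it to use before randomisation. Tabulate on-treatment use by arm.
3. Report the adjusted result as a marginal rate difference with 95% CI, from a stratified method or standardised logistic regression, against −10 points.
4. State which analysis, adjusted or unadjusted, decides non-inferiority, and make the mandatory and exploratory statements on covariates agree.

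Removing the Table 2 P values is optional. The cost is wording and a slight loss of analyst flexibility; no new data or patients are needed.
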